## Methods/Design

### Design

LC-REHAB was launched in three hospital units in Regional Hospital West Jutland (RHWJ), Denmark as an open randomised parallel group controlled study within which participants are allocated to either the intervention arm (LC strategies incorporated in standard CR) or to the control arm (standard CR). The randomisation is computer generated in a 1:1 ratio stratified for hospital unit, diagnosis (IHD or HF) and gender, alternating in blocks of two to four. According to power calculations, a total of 750 patients were needed to be recruited for the primary analysis. For secondary analysis of body compositions with Dual energy X-ray absorptiometry (DXA) scans, n = 150 patients were needed.

The CR program in both the intervention and control arms lasts for eight weeks, with training sessions three times a week and one education session per week. All sessions last 1.5 hours. In total, there are 24 training sessions and eight education sessions. The education in both arms is divided into eight topics; one topic per week. The topics are: function and symptoms of the heart, lifestyle effects on the development of IHD and HF, emotional reactions, medication, tiredness, the importance of relatives or other networks, importance and types of exercise, and future life with a chronic disease. The topics were elected on a theme day by LC educated health professionals and experienced patients with ‘The Disease Management Program for cardiovascular disease’ from Central Denmark Region as a general framework [18]. The training sessions are conducted by a physiotherapist in the presence of a nurse in case patients become unwell. The sessions consist of both cardio-stress and muscle-strengthening exercises. The education sessions are presented mainly by a nurse except for the topics on exercise and future life which are presented by the physiotherapist. In each arm of the study, patients are supported by the same team of nurse and physiotherapist throughout the eight week period.

Data is collected four times: at baseline, just after finishing the eight week CR program, three months after program completion, and at three years after program completion. A bicycle exercise test is conducted at all four data collection points (Figure 1).

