### Recruitment/settings

Study information is sent by mail to eligible patients and they are informed of the study via telephone by this paper’s first author. Informed consent is obtained one to two weeks after discharge by health professionals working in the CR units; either a nurse or a physiotherapist.

All CR programs start the first working day after randomisation and are performed in the CR units at each of the three hospitals. The majority of measurements are taken by health professionals or via questionnaires. Laboratory testing is performed at the hospitals’ laboratories, and DXA scans are performed at the Department of Nuclear Medicine within two of the three hospitals.

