### Outcomes

The primary outcomes are adherence to CR, morbidity and mortality. Secondary outcomes are quality of life as well as lifestyle and risk factors. Socioeconomic variables and other relevant characteristics are collected at baseline.

Adherence to CR is assessed as completing the CR program, defined as having performed the second exercise bicycle test at the end of the program as well as determining the proportion of attended versus planned training and education sessions. Morbidity and mortality data will be drawn from the Danish National Patient Registry and the Danish CPR-registry. All readmissions after randomisation regardless of diagnosis will be included as the intervention is aiming more broadly than only heart disease-related events. Readmissions for IHD or HF as a sub-measure will also be assessed. Survival is measured as a combined endpoint of death, readmission with acute coronary syndrome, revascularisation or unstable angina. Data on medication compliance will be drawn from the Danish national medication profile as an independent variable.

Quality of life is measured with Short Form-12, version 2 (SF-12) questionnaire [43]. Furthermore, SF-6D is measured; this is a preference based measure of health derived from the SF-12 and often used as quality-adjusted life years (QALY) [44]. The Health education Impact questionnaire, version 3 is used to measure the patients’ coping ability. This is a questionnaire with high validity and reliability developed in Australia to evaluate the impact of patient education programs [45, 46]. Depression is assessed with the Major Depression Inventory. This questionnaire is validated in a Danish trial and has good accordance with depression diagnosis made by a psychiatrist [47].

Self-reported lifestyle and risk factors are measured with questionnaires on diet, smoking and exercise. Weight, height and waist circumference are measured by health professionals at all data collection times. Body composition of fat, muscle and bone are determined by DXA scans. Blood pressure is measured in a sitting position after 5 minutes of rest. Exercise work capacity is estimated from a maximum symptom-limited exercise test on a bicycle ergometer starting with 25 watts, adding 25 watts every 2 minutes. Lipid profiles include fasting triglycerides, total cholesterol, LDL-cholesterol and HDL-cholesterol.

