## Discussion

In the future, increasing numbers of people will have to live with a chronic heart condition. Cardiac rehabilitation is thus of great significance due to its known potential to reduce morbidity and mortality and improve quality of life. Different patient education methods have been developed to address the challenges of non-adherence to CR programs and limited success with lasting lifestyle improvements. In the LC-REHAB study, the effect of a new patient education strategy; learning and coping, in addition to standard CR is evaluated on morbidity, mortality, adherence, quality of life plus lifestyle and risk factors. To understand the study design and rationale more comprehensively, knowledge of LC and the theory underlying its strategies is required. This paper combines a description of LC strategies and their theoretical basis along with the LC-REHAB study protocol.

Patients are followed up to three years after they have finished CR. This will provide insight into the long-term effect of CR and especially the effect of the LC strategies. The study is un-blinded. Combined with the self-reported information of quality of life, diet, smoking and exercise this may lead to differential misclassification.

This paper aims to provide knowledge and transparency of the theories behind LC strategies. The hypothesis is that LC strategies applied in CR can enhance adherence in CR and thus lead to reduced morbidity, morbidity and readmissions, and improve quality of life for patients with IHD or HF. Additionally, the results of the study will be a significant contribution to the development of relevant evidence-based guidelines for effective CR.

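### Open-label bias is acknowledged only for self-reports, although waist, and apparently also the effort-dependent bicycle test and blood pressure, are taken by staff with no stated masking to arm

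*Protocol article*

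**What the plan says.** The Design section describes the trial in "Denmark as an open randomised parallel group controlled study", and the Discussion states "The study is un-blinded", with no exception for outcome assessors. The Discussion then says where this may cause bias: "Combined with the self-reported information of quality of life, diet, smoking and exercise this may lead to differential misclassification". No measured outcome is mentioned there.

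On who measures, Recruitment/settings says "The majority of measurements are taken by health professionals or via questionnaires". It then places laboratory testing in the hospital laboratories and DXA in Nuclear Medicine. The Outcomes section is specific for one group of measurements: "Weight, height and waist circumference are measured by health professionals at all data collection times". Two others are described without naming who performs them: "Blood pressure is measured in a sitting position after 5 minutes of rest" and "Exercise work capacity is estimated from a maximum symptom-limited exercise test on a bicycle ergometer starting with 25 watts, adding 25 watts every 2 minutes". According to Design, the bicycle test is done at all four data collection points, and one nurse and physiotherapist team stays with a group for the eight weeks.

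**The concern.** A symptom-limited maximum test ends when patient and tester agree that it ends, so the result depends partly on how hard the patient is urged. Waist and sitting blood pressure also leave room for the observer, though less. If the person running the end-of-program test has spent eight weeks delivering one of the two programs, the conduct of the test can differ systematically between arms.

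A caveat that covers only self-reports invites the reader to treat work capacity, waist and blood pressure as free of open-label bias. A difference in work capacity could then be presented as a gain in fitness when part of it reflects how the test was conducted.

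**Working it through.** **1. Who takes what, section by section**

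| Measurement | Who, according to the article | Masking stated |
|---|---|---|
| Weight, height, waist | health professionals (Outcomes) | none |
| Blood pressure | not named (Outcomes) | none |
| Bicycle test | not named (Outcomes) | none |
| Lipids | hospital laboratories (Recruitment/settings) | none, but outside the CR team |
| DXA | Nuclear Medicine, two hospitals (Recruitment/settings) | none, but outside the CR team |
| SF-12, diet, smoking, self-reported exercise | patient | bias acknowledged in the Discussion |

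The preceding paragraph of Recruitment/settings uses the same term for CR-unit staff: "Informed consent is obtained one to two weeks after discharge by health professionals working in the CR units; either a nurse or a physiotherapist". That sentence concerns consent, not measurement. Because only laboratory tests and DXA are placed elsewhere, CR-unit staff are the natural reading for the bicycle test and blood pressure. This remains an inference.

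**2. Why change scores do not help**

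Let the follow-up test carry a tester effect b(LC) in one arm and b(C) in the other, and assume that the baseline test carries none that differs by arm. The expected difference in mean change is then

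true effect + [b(LC) − b(C)].

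The bracket arises after baseline, so the unpaired t-test on change in Statistical methods leaves it in place.

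**3. The plan's own sample size, to fix n**

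n per arm = 2 × (SD/difference)² × (1.960 + 0.842)², two-sided 5%, 80% power.
- Vitality: 2 × (24.4/5)² × 7.85 gives 374 per arm, 748 in total.
- Mental health: 2 × (13.4/2.75)² × 7.85 gives 373 per arm, 746 in total.

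Both agree with the stated 750. So n = 375 per arm, or 300 per arm at the article's 20% dropout.

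**4. Illustration only**

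The documents give no SD for work capacity and no size for the bias; both are assumed here. With no true effect and a bias of b SDs,

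P(reject) = Φ(b/SE − 1.96) + Φ(−b/SE − 1.96), SE = √(2/n).

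| Assumed bias (SD) | 375 per arm | 300 per arm |
|---|---|---|
| 0 | 5.0% | 5.0% |
| 0.05 | 10.5% | 9.4% |
| 0.10 | 27.8% | 23.2% |
| 0.15 | 53.7% | 45.1% |
| 0.20 | 78.2% | 68.8% |

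In watts: one stage is 25 W. If a net 1 in 10 patients in one arm went one stage further, the mean shift would be 0.1 × 25 = 2.5 W; for 1 in 5 it would be 5 W. With an assumed SD of change of 30 down to 20 W:
- 375 per arm: 21% to 40% for 2.5 W, and 63% to 93% for 5 W.
- 300 per arm: 18% to 33% for 2.5 W, and 53% to 86% for 5 W.

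The formula is symmetric, so a bias against LC gives the same figures in the other direction. The table shows that a small bias matters at this sample size. It does not show that one exists.

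**The case against.** A reader might infer that the treating teams do run these tests and that the results will favour LC. The documents do not support that.
- No tester is named for the bicycle test or blood pressure, and no measurement is tied to the patient's own team.
- The remark under LC strategies about extra effort concerns training alongside experienced patients, not testing. Fitness gained that way would be a genuine effect of the intervention.
- Motivational interviewing is described as the basis of the interviews and group sessions, not of the test.
- The same-team arrangement covers only the eight weeks, so nothing links a team to the tests at three months and three years.

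It can also be said that the article condenses a fuller protocol, where tester rosters and test procedures would normally be found, and that the Discussion nowhere claims the measured outcomes are unbiased. The false-positive figures largely restate the bias that was assumed. Morbidity and mortality come from registries, so these primary outcomes are not touched by who takes the measurements.

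All of this stands, and it limits the point. It does not remove what the article itself states: the study is un-blinded without exception, the outcomes include an effort-dependent test and a waist measurement by health professionals, and the bias discussion stops at self-reports. That discussion is too narrow whatever the full protocol says about testers.

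**Conclusion.** The point holds in a limited form. The caveat in the Discussion is narrower than the open design warrants. Waist certainly, and the bicycle test and blood pressure apparently, are taken by staff for whom no masking to arm is stated. Work capacity at the end of the program is the most exposed, because it depends on effort and is measured when contact with the team is closest. If the patient's own team runs that test, a difference in how it is conducted would pass straight into the comparison of changes.

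Neither the size nor the direction of such a bias can be taken from the documents. The illustrative error rates rest wholly on an assumed SD and an assumed shift. Lipids and DXA are largely exempt, so the concern does not extend to all measured secondary outcomes. This is an inexpensive improvement to make, not a threat to the registry outcomes.

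**What to change.** 1. State who performs the bicycle test and who measures blood pressure and waist, and whether they know the arm.
2. For follow-up, have existing CR staff who are not on the patient's own team take these measurements, with the same testers serving both arms where possible. Randomisation is stratified by hospital unit and the study uses eight programs, four per arm, so staff outside any one patient's team should be available without new assessors.
3. Leave the arm off the test form, and use one written instruction and encouragement script in both arms. This standardises wording only; clinical grounds for ending a test are not altered.
4. Extend the Discussion caveat to staff-taken measurements, so that a difference in work capacity is not presented as free of open-label bias.

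When rosters change, make sure the second bicycle test is still offered equally in both arms, because having performed it defines completion of CR under Outcomes and so enters the primary adherence outcome.

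The cost is some scheduling effort and a short script. Masking will be imperfect, since staff in one unit may know which program a patient attends. Recruitment began in November 2010, so some tests may already have been done; the wider caveat can be added regardless.

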### Power calculations

From an existing CR database in RHWJ the standard deviation (sd) on the change in the SF-12 scales was known. It is expected that better coping ability could affect the scales ‘vitality’ (sd = 24.4 percentage points) and ‘mental health’ (sd = 13.4 percentage points). Necessary participant numbers were calculated under different assumptions which led us to choose a sample size of minimum 750 patients. If all patients complete the program, a difference in vitality of 5 percentage points and a difference in mental health of 2.75 percentage points will be detected with a power of 80% and a p-value of 0.05. With a dropout of 10 and 20% respectively, a difference in vitality of 5.3 and 5.6 respectively, and a difference in mental health of 2.9 and 3.1 respectively, will be found under the same assumptions.

From in vivo precision of DXA scans a sd of 0.187 in total body fat (TBF) at two consecutive measures was known [48]. We will include at least 150 patients to receive DXA scans in this study. Selection was based on the computer generated randomisation, thus every fourth participant was allocated for DXA scan – stratified for two hospital units, gender and diagnosis. If all 150 patients attend the DXA scan a difference of 0.09 kg in TBF will be able to be shown with a power of 80% and a p-value of 0.05.

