### Statistical methods

Data is entered into dedicated databases and statistical analysis will be performed using STATA13 [49]. Cleaning and data management will be carried out on all relevant datasets and all statistical analysis will be performed using the ‘intention to treat’ principle. Descriptive statistics will be used to describe baseline variables. Differences in change in mean scores from baseline to follow-up between the two groups for continuous variables will be tested using unpaired t-tests provided they are normally distributed. Non-parametric tests will be performed for non-normally distributed data. Multiple regression analysis will be undertaken to check for interactions between gender, age and socio-economic background. For dichotomous variables, chi-square tests or logistic regression will be performed. Readmissions and survival will be analysed using Cox regression analysis.

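### An unpaired t-test on change scores cannot by itself deliver the stated intention-to-treat analysis when missing follow-up is tied to completion, which the intervention is meant to raise

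*Protocol article*

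**What the plan says.** Four parts of the protocol article bear on this point.

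- **Statistical methods** sets the principle, "all statistical analysis will be performed using the ‘intention to treat’ principle", and the test: "Differences in change in mean scores from baseline to follow-up between the two groups for continuous variables will be tested using unpaired t-tests". A non-parametric test replaces the t-test where data are not normal. The section does not say what happens to a patient with no follow-up value.
- **Power calculations** bases the trial's size on two SF-12 scales, vitality ("sd = 24.4 percentage points") and mental health (SD of change 13.4). The calculations "led us to choose a sample size of minimum 750 patients". If everyone completes, the detectable differences are 5 and 2.75 points. Then: "With a dropout of 10 and 20% respectively, a difference in vitality of 5.3 and 5.6 respectively", with 2.9 and 3.1 for mental health.
- **Outcomes** names adherence, morbidity and mortality as primary. Adherence is measured by completion, "defined as having performed the second exercise bicycle test at the end of the program", and by the share of planned sessions attended. Quality of life, lifestyle and risk factors, including work capacity from the bicycle test, are secondary.
- **Design** places a bicycle test at all four data collections and dates the later visits from the end of the program. **Discussion** gives the hypothesis that LC improves adherence.

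**The concern.** A change score needs two measurements, so a patient without a follow-up value cannot enter the named test unless something is added to it. That would be a matter of precision alone if missing follow-up were unrelated to treatment. Here the trial's own hypothesis is that treatment affects completion.

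If LC keeps patients who would have left under standard rehabilitation, those patients contribute to the LC mean while their counterparts are absent from the control mean. The two analysed groups are then no longer the two randomised groups.

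For work capacity at the end of the program the overlap is built in. One event, doing the second bicycle test, is both the definition of completing and the condition for having the measurement.

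At stake are the secondary continuous outcomes: the quality-of-life scales on which 750 patients were chosen, work capacity and the measured risk factors. If the patients LC retains improve less than average, the distortion runs against LC and could hide a benefit.

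**Working it through.** **1. Reproduce the plan's own figures.** Inputs are all from the protocol article: 750 patients and the SDs of 24.4 and 13.4 (Power calculations), 1:1 allocation (Design), 80% power and 0.05 (Power calculations). Sidedness is not stated; two-sided is used here.

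Detectable difference = (1.960 + 0.842) × SD × √(2/n), with n = 375 × (1 − dropout) per arm.

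| Dropout | n per arm | Vitality, computed | Stated | Mental health, computed | Stated |
|---|---|---|---|---|---|
| 0% | 375 | 4.99 | 5 | 2.74 | 2.75 |
| 10% | 337.5 | 5.26 | 5.3 | 2.89 | 2.9 |
| 20% | 300 | 5.58 | 5.6 | 3.07 | 3.1 |

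The stated figures are correct. A one-sided 0.05 would give 4.43, 4.67 and 4.95 for vitality and does not match. The figures reproduce with dropouts removed from n and one rate applied to both arms. In this calculation dropout costs precision and nothing else.

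**2. Bias when only patients with follow-up are compared.** Suppose there is no true effect, so both arms have the same mean change μ over all randomised patients. Let d be the share without follow-up and g the mean change of those observed minus that of those not observed. Then μ = (1 − d) × observed mean + d × (observed mean − g), so the observed mean is μ + d × g. With the same g in both arms:

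Bias (LC minus control) = (d in LC − d in control) × g.

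**3. Illustration.** The article gives no dropout by arm and no value of g. Its two dropout scenarios are assigned here, by assumption, as 10% in LC and 20% in control. The difference g is assumed to be 0.25, 0.5 or 0.75 SD.

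- Vitality: −0.10 × 6.1 = −0.61; −0.10 × 12.2 = −1.22; −0.10 × 18.3 = −1.83. Against the planned 5 points this is 12%, 24% and 37%.
- Mental health: −0.34, −0.67 and −1.01, the same proportions of 2.75.
- The standard error for vitality is 24.4 × √(1/337.5 + 1/300) = 1.94, so the two-sided type I error becomes about 6%, 10% and 16% instead of 5%.

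**4. Equal dropout is not sufficient protection.** If both arms lose a share d but for different reasons, bias = d × (g in LC − g in control). With d = 20%, g = 0 in LC and 0.5 SD in control, vitality shifts by 0.20 × (0 − 12.2) = −2.44 and mental health by −1.34.

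**5. When there is no bias.** If dropout shares and reasons are the same in both arms, both expressions give zero. If those who leave do better than those who stay, g is negative and the sign in step 3 reverses.

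**The case against.** The strongest reply is that the article never says patients without follow-up are excluded. It names a test and a principle. A t-test can be run on imputed change scores, missing-data handling is commonly left to an analysis plan that is not shown, and cutting n for dropout is routine planning whatever analysis follows. All of this is fair, and it limits the point. What stands is that the article does fix a method, and that method alone does not reach every randomised patient. Any further document would have to supplement or replace it.

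Four stronger readings are tempting but not supported.

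- A reader might infer that the analysis is not intention to treat. The article states the opposite, and comparing patients as randomised is compatible with a t-test. The supportable statement is that the test alone cannot deliver the principle for all randomised patients.
- A reader might infer that dropout is itself the primary outcome. Completion is one of two adherence measures, and adherence is one of three primary outcomes.
- A reader might infer that non-completers leave the study. Nothing says so. Quality of life is collected by questionnaire and there are visits at three months and three years, so non-completers may still be measured. The definitional link covers only the bicycle test at the end of the program.
- A reader might take the power figures to be wrong. They are right.

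It is also true that a mixed model assumes data missing at random and so does not by itself remove selection. That is why a sensitivity analysis belongs with it.

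**Conclusion.** The concern holds in a limited form. The continuous secondary outcomes, including the scales behind the sample size, are assigned a test that alone uses only patients with follow-up. The trial's hypothesis links completion, and hence plausibly follow-up, to treatment. For end-of-program work capacity the link follows from the definition of completion. The intention-to-treat statement does not resolve this, and Power calculations considers only lost precision.

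The document supports neither a size nor a direction for the bias. The range of about −0.6 to −1.8 points on vitality, against LC, rests entirely on the assumed 10% and 20% dropout, a deficit of 0.25 to 0.75 SD common to both arms, and no true effect.

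Readmissions and survival come from national registries, and completion and session attendance can be scored for every randomised patient, so those analyses are untouched. This should be changed, but it does not threaten the primary outcomes.

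**What to change.** 1. In Statistical methods, replace the t-test on change with a baseline-adjusted mixed model for repeated measures over the planned time points. Include arm-by-time and the stratification factors (hospital unit, diagnosis, gender), and all randomised patients with any measurement. Modelling baseline as one of the measurements, with a common mean across arms, keeps patients who have only a baseline value. Multiple imputation using session attendance and baseline variables is an acceptable alternative.
2. Add a delta-shift sensitivity analysis in which the unobserved outcomes of non-completers are made progressively worse or better, separately by arm.
3. State that the planned questionnaires and the three-month and three-year visits are sought from every randomised patient, completer or not, and dated from the scheduled end of the program, so that the visit date is defined for non-completers.
4. If end-of-program change in work capacity is shown in completers only, label it a non-randomised comparison.

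The cost is wording, modest extra modelling, and follow-up contact through visits and questionnaires already planned. The sample size need not change. The main model brings a missing-at-random assumption, which the delta-shift analysis probes.

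### The DXA power statement uses scanner repeatability (0.187) where the planned analysis needs the between-patient SD of change, so the 0.09 kg detectable difference is too optimistic

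*Protocol article*

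**What the plan says.** The second paragraph of Power calculations in the protocol article sizes the DXA sub-study. It gives the planning SD and its source: "From in vivo precision of DXA scans a sd of 0.187 in total body fat (TBF) at two consecutive measures was known". It sets the number: "We will include at least 150 patients to receive DXA scans in this study". It then states what that number achieves under full attendance: "a difference of 0.09 kg in TBF will be able to be shown with a power of 80% and a p-value of 0.05". The Design section presents the same 150 as the number required for the secondary body-composition analysis.

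Two other places matter. Statistical methods says that continuous outcomes are analysed by comparing mean change from baseline between the two groups, with unpaired t-tests where the data are normally distributed. The first paragraph of Power calculations, on the SF-12, takes its SDs from the change in the scale scores in an existing local rehabilitation database.

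**The concern.** Precision from repeat scans describes how much two readings differ when the person has not changed. It is measurement error only. A comparison of change between arms also carries the variation in true fat change among patients, some of whom lose fat over an exercise programme while others gain. The earliest follow-up in the Design section is at the end of the eight-week programme, and later ones come three months and three years after it, so true change has time to differ between patients.

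The SF-12 half of the section uses the right kind of SD for this analysis and the DXA half does not. This is the only justification given for the size of the sub-study. If the figure stands, the sub-study is credited with a sensitivity that its design does not have, and a reader could lean on that figure when judging a body-composition result.

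**Working it through.** **Inputs**
- SD 0.187, from Power calculations. No unit is printed; kg is implied by the result.
- 150 patients, from Power calculations. The Design section says "The randomisation is computer generated in a 1:1 ratio", so 75 per arm.
- Power 80% and significance level 0.05, from Power calculations. Sidedness is not stated; two-sided is taken first.
- No dropout: "If all 150 patients attend the DXA scan".

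**Formula.** Detectable difference = SD × √(2/75) × (1.960 + 0.842) = SD × 0.1633 × 2.802 = SD × 0.4575.

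**Step 1: reproduce the plan's figure.** 0.187 × 0.4575 = 0.0856 kg, which rounds to the stated 0.09 kg (0.0861 kg with the t distribution). The alternatives do not give 0.09:
- one-sided: 0.187 × 0.1633 × (1.645 + 0.842) = 0.076 kg, which rounds to 0.08;
- 0.187 treated as the error of one scan, so that a difference of two scans has SD √2 × 0.187 = 0.264: 0.264 × 0.4575 = 0.121 kg, which rounds to 0.12.

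So 0.187 was entered as it stands as the SD of the compared outcome.

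**Step 2: check that the SF-12 part uses the same formula.** With 375 per arm, 24.4 × √(2/375) × 2.802 = 4.99 and 13.4 × √(2/375) × 2.802 = 2.74, against the stated 5 and 2.75. Solved for sample size, the totals are 748 and 746, against the stated minimum of 750. The method is the same and only the kind of SD differs.

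**Step 3: what 0.09 kg would require, using the document alone.** Take 0.187 as the SD of a difference between two scans, and let 0.09 stand for anything up to 0.095. The total SD can then be at most 0.095 / 0.4575 = 0.208. The room left for true differences in fat change is √(0.208² − 0.187²) ≈ 0.09 kg. Under normality about 95% of patients in an arm would have to lie within 1.96 × 0.09 ≈ 0.18 kg of the arm's mean change. If 0.187 is instead a single-scan error, step 1 shows that scanner noise alone gives 0.12 kg, and 0.09 kg is missed even if every patient in an arm changes by the same amount.

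**Step 4: the size under assumed SDs of change.** The SDs below are assumptions; none stands in the document. Power for 0.09 kg is Φ(0.09 / (SD × 0.1633) − 1.96) plus the small opposite tail. Total N is 2 × 2 × 2.802² × SD² / 0.09², rounded up per arm.

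| Assumed SD of change (kg) | Detectable difference, n = 150 (kg) | Ratio to 0.09 | Power for 0.09 kg | Total N for 0.09 kg |
|---|---|---|---|---|
| 0.5 | 0.23 | 2.5 | 19.7% | 970 |
| 1 | 0.46 | 5.1 | 8.5% | 3,876 |
| 2 | 0.91 | 10.2 | 5.9% | 15,504 |
| 3 | 1.37 | 15.2 | 5.4% | 34,884 |

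The detectable difference is twice the stated one at SD 0.18 / 0.4575 = 0.39 kg, and three times at 0.27 / 0.4575 = 0.59 kg.

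**The case against.** The strongest reply is that the size of the error cannot be read from the document. A reader might infer that the stated figure is wrong by several fold. That holds only if the SD of change is large enough: the factor is 2 at 0.39 kg and reaches 3 only at about 0.59 kg. With no SD of change printed, the multiple is an assumption. This stands, and the size is therefore given here as a range. It does not rescue 0.09 kg, because step 3 shows that the figure needs almost no variation in true fat change.

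A second reply is that the calculation itself is sound. That also stands: 0.0856 rounds to 0.09, and the fault is the choice of input.

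A third is that the planning SD does not enter the analysis. The t-test and its confidence interval use the observed SD, so their validity is untouched. Nor does the article say that a null result will be taken to exclude 0.09 kg. Both are true, and what remains is a false statement of sensitivity.

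A reader might also infer that 150 cannot be reached, because "every fourth participant was allocated for DXA scan" while "DXA scans are performed at the Department of Nuclear Medicine within two of the three hospitals". One in four gives 150 if those two units recruit 600 of the 750. The document gives no recruitment by unit, and both 750 and 150 are stated as minimums, so no shortfall is shown.

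**Conclusion.** The point holds as a wrong planning input. Scanner repeatability was used as the SD for a between-arm comparison of change, and the claim of 80% power for 0.09 kg with 150 patients is too optimistic. The text and the reproduced arithmetic both establish this. How far it is off rests on an SD that the document does not supply: for assumed values from 0.5 to 3 kg the detectable difference is about 0.23 to 1.37 kg, with power for 0.09 kg of about 20% at 0.5 kg and below 10% from 1 kg. These figures assume 75 per arm, a two-sided 0.05 level and no missing scans.

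The statement should be corrected, but its reach is limited. DXA is a secondary outcome in a subset. It would be wrong to infer that the trial's main sample size is in doubt, since the 750-patient calculation is separate and reproduces.

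**What to change.** Replace the 0.09 kg sentence with the detectable difference computed from an SD of change in total body fat, and stop using the precision SD as the planning value. One source would be the trial's own paired scans once available, pooled over arms and summarised without looking at the group difference. The document does not say how many pairs exist, so until then give the detectable difference over a stated range of assumed SDs, as in the table, and label it as an assumption. Reword the Design section so that 150 is not presented as the number needed to show 0.09 kg.

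The cost is a few sentences. No extra scans, patients or change of analysis are needed. The downside is that the sub-study's stated sensitivity becomes less favourable.
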